#### Benzodiazepine reduction

Withdrawal of benzodiazepines in intervention patients will follow recommendations from the Society of Critical Care Medicine (SCCM) guidelines regarding the use of sedative and analgesic medications in critically ill patients [4]. Benzodiazepine reduction will occur cautiously but deliberately, with constant communication with the primary medical or surgical team and with close monitoring for intolerable withdrawal reactions. Benzodiazepine dose reductions will be initiated with 20-40% dose reduction on day one, with subsequent reductions of 10-25% every 24 hours as tolerated. Safety and tolerability of the weaning schedule will be evaluated through routine nursing assessments of vital signs and behavior documented every four hours.

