In our study an adverse event will be defined as any untoward medical occurrence in a subject without regard to the possibility of a causal relationship. Adverse events will be collected after the subject has provided consent and enrolled in the study. If a subject experiences an adverse event after the informed consent document is signed (entry) but the subject has not started to receive study intervention, the event will be reported as not related to study drug. All adverse events occurring after entry into the study and until hospital discharge will be recorded. An adverse event that meets the criteria for a serious adverse event (SAE) between study enrollment and hospital discharge will be reported to the local IRB as an SAE. If haloperidol is discontinued as a result of an adverse event, study personnel will document the circumstances and data leading to discontinuation of treatment. A serious adverse event for this study is any untoward medical occurrence that is believed by the investigators to be causally related to study-drug and results in any of the following: Life-threatening condition (that is, immediate risk of death); severe or permanent disability, prolonged hospitalization, or a significant hazard as determined by the Data Safety Monitoring Board. Serious adverse events occurring after a subject is discontinued from the study will NOT be reported unless the investigators feels that the event may have been caused by the study drug or a protocol procedure. Investigators will determine relatedness of an event to study drug based on a temporal relationship to the study drug, as well as whether the event is unexpected or unexplained given the subject's clinical course, previous medical conditions, and concomitant medications.

Although haloperidol is widely used in treatment of delirium, it is not approved by the FDA for such use, and its efficacy in such treatment is not clear. Although our study employs a low dose (1.5 mg per day) of haloperidol for a short period of time (seven days), its potential adverse effects of QT prolongation and extrapyramidal symptoms (EPS) will be monitored during the study. The study will monitor for the following movement-related adverse effects daily through patient examination and chart review: dystonia, akathisia, pseudoparkinsonism, akinesia, and neuroleptic malignant syndrome. Study personnel will use the Simpson-Angus [46] and Barnes Akathisia [47] scales to monitor movement-related effects.

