#### Data Safety Monitoring Board

A data safety monitoring board (DSMB) consisting of five members having no participation in the planning or execution of the study will be assembled. The DSMB will be responsible for the oversight of the safety of study patients and to ensure an appropriate sample is collected throughout the study period. The board will review relevant safety data after the completion of data collection of 25%, 50%, and 75% of the planned study sample. During these safety analyses, the DSMB will make recommendations to continue or terminate the progress of the study based on the observed effects of the study intervention.

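### The serious adverse event definition requires investigator-believed causality to study drug and does not list death, so SAE classification and IRB reporting would be asymmetric between arms and would leave out two of the three intervention components

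*Protocol article*

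**What the plan says.** All of the relevant definitions stand in the adverse event text under Secondary Outcomes in the protocol article.

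- An adverse event is "any untoward medical occurrence in a subject without regard to the possibility of a causal relationship". All such events are recorded from entry to hospital discharge.
- A serious adverse event means "any untoward medical occurrence that is believed by the investigators to be causally related to study-drug and results in any of the following". Four outcomes then qualify, and death is not among them. Events meeting both conditions go to the local IRB as SAEs.
- The list of outcomes reads "Life-threatening condition (that is, immediate risk of death); severe or permanent disability, prolonged hospitalization, or a significant hazard as determined by" (a judgement left to the DSMB).
- For events after consent, if "the subject has not started to receive study intervention, the event will be reported as not related to study drug".
- On attribution: "Investigators will determine relatedness of an event to study drug based on a temporal relationship to the study drug". The investigators also consider whether the event is unexpected or unexplained given the clinical course, history and other medication.
- Serious events after a subject is discontinued are not reported "unless the investigators feels that the event may have been caused by the study drug or a protocol procedure".

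Elsewhere, the section on benzodiazepine reduction describes a taper with "close monitoring for intolerable withdrawal reactions". The haloperidol section limits the order to intervention patients not under mechanical ventilation, and withholds the drug for a long QT interval, a seizure history or an indication for seizure prophylaxis. The Usual Care section lets control patients receive haloperidol as routine care.

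**The concern.** Seriousness and relatedness are separate attributes of an event. Here the second decides whether the first can apply. An event that threatens life is not serious, in the protocol's sense, unless an investigator also believes that study drug caused it.

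Three consequences follow. Control patients are assigned no study drug, so hardly any of their events can qualify. The intervention has three components, and only one of them gives a drug; harm from withdrawing or avoiding drugs has no clear route into the definition. And a death is not serious merely because it is a death.

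What is at stake is the set of events labelled and reported as SAEs. A table of SAEs by arm would reflect the definition and the attribution habits of the investigators rather than the frequency of serious events. The IRB would receive an incomplete account of serious harm from the taper and from anticholinergic reduction.

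**Working it through.** The plan states no SAE rate or count, so there is no figure to reproduce. The check is a reading of the rule against the rest of the article, followed by an illustration of size.

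**Step 1: what study drug covers.** The term is not defined. Haloperidol is the only drug that the protocol itself gives; the other two components reduce anticholinergics and benzodiazepines. The post-discontinuation rule names study drug and protocol procedure as alternatives, which suggests that study drug was not meant to include everything the protocol does. The plain reading is haloperidol.

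**Step 2: apply the written rule to each kind of event.**

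| Event with a serious outcome | SAE under the written rule? | Reason |
|---|---|---|
| Intervention arm, attributed to haloperidol | Yes | Meets both conditions |
| Intervention arm, caused by the benzodiazepine taper | No, on the plain reading | Not caused by study drug, although withdrawal reactions are foreseen |
| Intervention arm, caused by anticholinergic reduction | No, on the plain reading | Same |
| Intervention arm, no haloperidol ordered or given | No, on the plain reading | No exposure to which the event can be attributed |
| Usual care, no haloperidol | No | No study drug; the study intervention never starts |
| Usual care, after routine haloperidol | Unclear | Depends on whether routine haloperidol counts as study drug |
| Death in either arm, not attributed to study drug | No | Causality condition fails, and death is not a listed outcome |

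**Step 3: consistency within the text.** The adverse event definition sets causality aside; the serious one requires it. The in-trial test is study drug alone; the later test is study drug or a protocol procedure. So a serious event caused by a protocol procedure is reportable after discontinuation but not during the trial.

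**Step 4: illustration of the asymmetry.** Inputs from the article: 428 patients, 1:1 allocation, so 428 / 2 = 214 per arm. Assumptions, not in the article: a true serious-event rate p, equal in both arms; a share f of intervention-arm events attributed to study drug, from 5% to 25%; and a usual-care count of zero as a limiting case.

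Events per arm by outcome alone = 214 × p. SAEs in the intervention arm as written = 214 × p × f.

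| p | Serious events in each arm | SAEs as written, intervention | SAEs as written, usual care (limiting case) |
|---|---|---|---|
| 10% | 21.4 | 1.1 to 5.4 | 0 |
| 20% | 42.8 | 2.1 to 10.7 | 0 |
| 30% | 64.2 | 3.2 to 16.1 | 0 |

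With no true difference between arms, the labelled counts differ, and most serious events carry no label in either arm.

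**The case against.** The strongest reply is that the harm data do not depend on the SAE label, and much of that reply stands.

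- All adverse events are recorded to discharge, and usual-care patients have twice-daily safety and adverse event visits.
- ICU, hospital and 30-day mortality are secondary outcomes. Mortality and complications are tested between arms by logistic regression with no causality filter.
- "The DSMB will be responsible for the oversight of the safety of study patients", and it reviews relevant safety data at 25%, 50% and 75% of the sample. Nothing confines that review to events labelled SAE.
- The interim harm tests use the primary analysis methods. In the duration outcome, days after a death before day 8 count as not coma-free or delirium-free, so early deaths enter whatever their attributed cause.
- No between-arm test of SAEs is planned; the label works as a trigger for IRB reporting.
- A fatal event attributed to study drug could enter as life-threatening or as a DSMB-determined hazard. The causality condition therefore matters more than the omission of death.

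What this leaves untouched is the definition itself. The listed complications (falls, restraints, pulled lines or catheters, re-intubation, pressure ulcers) do not include withdrawal events or arrhythmia. The interim tests concern delirium outcomes, not serious events. The article does not commit to a causality-free count of serious events by arm. Nor is this a matter left to a fuller document: the article prints a complete rule, and the rule is the problem.

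**Conclusion.** The definition is wrong as written and should be changed. It contradicts the causality-free adverse event definition beside it and is narrower than the protocol's own post-discontinuation test. On the reading that study drug means haloperidol, any SAE count by arm would be asymmetric by construction. The damage is confined to SAE classification and IRB reporting; the primary outcomes, the mortality comparison and the interim harm tests are not affected. The size in counts is illustrative only, because the documents give neither a serious-event rate nor an attribution share.

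A reader might infer more than the documents support:

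- That the DSMB would miss deaths, or that an excess of serious harm would pass unseen. Deaths and adverse events are captured by other routes in both arms.
- That usual-care patients cannot have an SAE. Routine haloperidol is allowed and study drug is undefined, so close to zero is as far as the text goes.
- That relatedness is judged with knowledge of the arm. The intervention is visibly delivered, so this is plausible, but the article does not say who is blinded.
- That expected deaths measure the flaw. Table 1 gives (40 × 11% + 67 × 12% + 228 × 1.3%) / 335 = 4.6%, about 20 ICU deaths in 428, or 47 to 51 at 11-12%. These are rates for all ICU admissions, not for delirious enrollees, and the deaths are counted as an outcome regardless of the SAE label.

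**What to change.** 1. Define a serious adverse event by outcome only, and list death among the outcomes.
2. Apply the same definition in both arms from randomization to hospital discharge.
3. Record relatedness in a separate field, with entries for haloperidol, the benzodiazepine taper and anticholinergic reduction. Define study drug, and state how routine haloperidol in usual care is treated.
4. Reconcile the in-trial wording with the post-discontinuation wording, so that the same causes are considered in both periods.
5. Give the DSMB all-cause SAEs by arm at its scheduled reviews.

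The cost is a wording amendment and a case-report-form field. Adverse events are already collected in both arms to discharge, and 30-day mortality is already an outcome, so no new data collection is needed. The downside is more SAE reports, many of them expected in critical illness.

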### Planned Analysis

#### Data Analysis

We will conduct intention-to-treat analyses to test the intervention effects on the primary outcomes. No interim analysis is planned for early termination due to efficacy. To formally test for potential harm due to the intervention, 3 interim analyses will be performed using the proposed primary analysis methods after the completion of 0.25, 0.5 and 0.75 of the projected 428 evaluable subjects, using the O'Brien-Fleming boundary, for an overall significance level of 0.05 at study completion.

To test the intervention effect on severity of delirium, we will use the primary outcome of DRS-R-98 severity score on day 8 post-randomization. The primary analysis to test the intervention effect on day-8 DRS-R-98 severity score will be analysis-of-covariance (ANCOVA) with the baseline score as a covariate, after testing and removing any intervention-by-baseline score interaction. If there is a significant interaction, we will test the intervention effect at the mean of the baseline DRS-R-98 severity score. We will use the last observed DRS-R-98 forward to Day 8 as the primary outcome in one analysis. For sensitivity analyses, we will use different methods to impute the missing data. For example, we will impute the missing Day 8 DRS-R-98 severity scores with their worst score on record for patients who have been discharged with delirium or died before day 8. For patients who were hospitalized but could not be evaluated for whatever reason on day 8, we could also interpolate their previous and subsequent DRS-R-98 severity scores to estimate the missing Day 8 score.

We will also test the intervention effect on the repeated measures of DRS-R-98 severity scores using a mixed-effects model. An appropriate contrast for the day 8 effect will be used to corroborate the results of the ANCOVA in the primary analyses. This analysis will provide additional information on the time course of the severity of delirium from its onset in the ICU, with or without intervention.

To test the intervention effect on duration of delirium, we will compare between groups the number of coma-free and delirium-free days in the first 8 days post-randomization using a two-sample t-test corroborated with the Wilcoxon rank sum test. The intervention effect will be further tested while controlling for patient characteristics using multiple regression. Patients who die before day 8 will have all subsequent days counted as not coma-free or delirium-free. We will impute all days post-discharge as coma-free and delirium-free.

For secondary outcomes, binary measures, e.g. mortality and complications, logistic regression will be used to test the intervention effect, controlling for covariates when appropriate. Highly skewed outcomes such as hospital and ICU length of stay will be compared between groups using nonparametric tests, such as Wilcoxon's rank sum test, and semiparametric survival analyses which can control for covariates.

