#### Low-Dose Haloperidol course

During the ICU stay, every patient who consents to the study, randomized into the intervention group, and is not under mechanical ventilation will received an order of 0.5 to 1 mg haloperidol every 8 hours via oral or parental route for a total of seven days or until discharge from the hospital. Because of age-related pharmacokinetic differences in metabolism and pharmacodynamic sensitivity, patients under the age of 60 years will be given 1 mg/dose, and those aged 60 years or older will be given 0.5 mg/dose. This low dose of haloperidol is based on the critical analysis of the data from the clinical trials that tested the use of antipsychotics in delirium and the drug metabolism of psychotropics in older adults. This low dose is not intended to replace the sedative regimen used in patients receiving mechanical ventilator.

Intravenous haloperidol use has been associated with a higher risk of cardiovascular adverse outcomes, specifically QT prolongation and Torsades de Pointe. However, in a recent systematic review of case reports of haloperidol-associated arrhythmias, a wide range of haloperidol doses were used prior to the inciting events (2-1540 mg). The onset of most events was typically within minutes to hours following the cumulative doses of haloperidol (range 15 minutes to 5 days). The authors concluded that haloperidol given intravenously appears safe when given in doses less than 2 mg. Patients enrolled in our study will not be given haloperidol if they have: (1) a QT prolongation of 500 milliseconds or above, (2) a history of seizure disorders, or (3) an indication for seizure prophylaxis (i.e., severe stroke or traumatic brain injury) as haloperidol may decrease the seizure threshold [34].

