#### Secondary Outcomes

The study will collect demographic and baseline functional information from the patient's legally authorized representative and/or caregivers. Cognitive function status will be obtained by interviewing the patient's legally authorized representative using the Informant Questionnaire on Cognitive Decline in the Elderly (IQCODE). IQCODE is a questionnaire that can be completed by a relative or other caregiver to determine whether that person has declined in cognitive functioning. The IQCODE lists 26 everyday situations where a person has to use their memory or intelligence. Each situation is rated by the informant for amount of change over the previous 10 years, using a Likert scale ranging from 1-much improved to 5-much worse. The IQCODE has a sensitivity between 69% to 100% and specificity of 80% to 96% for dementia [41].

Utilizing the electronic medical record system (RMRS), we will collect several data points of interest at baseline and throughout the study period. First, RMRS will allow us to collect reason for admission, severity of illness (APACHE II) [42], and the number of comorbid conditions (Charlson Comobidity Index) [43] for each patient enrolled in the study. We will also collect length of stay (both ICU and total hospital stay), mortality rate, and hospital-related consequences. We have previously defined hospital-related consequences to include: the number of patients with documented falls, use of physical restraints, injuries such as pulling out IV lines or urinary catheters, any ordered or observed re-intubation, and pressure ulcers. These will be assessed using the RMRS, direct daily observation, and retrospective review of the electronic medical record. This definition of delirium-related hospital complications has been previously used and published [44,45].

Use of all medications, including focused intervention-related medications (anticholinergics, benzodiazepines, and haloperidol) will be monitored through the GOPHER computerized order entry system, as well as the McKesson medication administration system. The McKesson system is used at the patient's bedside and collects the administration of each medication. Additionally, McKesson is able to monitor medications administered as continuous infusions by documenting start times, stop times, and drip rates throughout the administration period.

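### The severity ANCOVA is valid but adjusts only for baseline DRS-R-98; pre-naming age and APACHE II, already collected, could add modest precision at little cost

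*Protocol article*

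**What the plan says.** In the protocol article, Data Analysis, the first primary outcome is "the primary outcome of DRS-R-98 severity score on day 8 post-randomization". The test is "analysis-of-covariance (ANCOVA) with the baseline score as a covariate", after a check for an intervention-by-baseline interaction. The last observed score is carried forward to day 8. A second analysis uses "repeated measures of DRS-R-98 severity scores using a mixed-effects model" to corroborate the result; its covariates are not stated.

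For the second primary outcome, coma-free and delirium-free days, the same section starts with an unadjusted t-test and Wilcoxon test and then adds: "The intervention effect will be further tested while controlling for patient characteristics using multiple regression". It also allows covariates in the models for the secondary outcomes.

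Under Secondary Outcomes, the article describes the patient data available: "The study will collect demographic and baseline functional information", and "RMRS will allow us to collect reason for admission, severity of illness (APACHE II"), with the Charlson index as well. ICU ward appears in the eligibility criteria but is not in that list of collected variables.

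The Randomization section gives 1:1 allocation in blocks of four and states no stratification factor.

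**The concern.** The severity model is an explicit choice, so the article is not merely silent on a detail. It uses one covariate although other baseline information is at hand, and severity is the only outcome class for which the article mentions no adjustment for patient characteristics.

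Age and acute illness severity may predict the day-8 score beyond what the baseline score already tells. If they do, leaving them out keeps their variation in the residual. The confidence interval for a primary outcome is then wider than it needs to be, and power is lower than the same patients could give.

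There is also a practical stake. If the arms happen to differ visibly in age or APACHE II, an adjusted severity analysis will be asked for. A list chosen after the data are seen carries less weight than one named in advance.

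**Working it through.** **Inputs from the article.** N = 428, allocated 1:1, so 214 per arm; overall significance level 0.05; ANCOVA with one covariate.

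**Assumptions, because the article gives no figure.**
- The 0.05 is two-sided, and the harm-only interim looks are ignored.
- Power under the planned model is 80%.
- R² is the share of the variance left after baseline score that the added covariates explain. The range taken is 0 to 0.15.

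**The plan's own figure.** The 428 cannot be reproduced, because the article gives no effect size, standard deviation or power. Working backwards, 214 per arm gives 80% power for a standardized difference of (1.960 + 0.842) × √(2/214) = 0.271 residual SD. This serves only as the starting point.

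**Step 1: is the planned model valid?** A simulation of 20,000 null trials used N = 428 in blocks of four and omitted a prognostic covariate with coefficient 0.35 against a residual SD of 0.8. That covariate holds 0.35² / (0.35² + 0.8²) = 16% of the variance left after baseline. The baseline-only ANCOVA gave a type I error of 0.048 and a mean estimate of −0.0007 (Monte Carlo SE 0.0006). There is no sign of bias or of alpha inflation.

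**Step 2: precision with added covariates.** The standard error is multiplied by √(1 − R²). The noncentrality becomes 2.802 / √(1 − R²), and power is Φ(noncentrality − 1.960). The equivalent sample size is 428 / (1 − R²). To charge for the extra terms, the residual variance is multiplied by 425 / (425 − k), where 425 = 428 − 3 and k is the number of added terms. The last column uses k = 5, which is generous for age, APACHE II and ward.

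| Assumed R² | SE reduction | Power, no charge | Equivalent N (extra) | Power, k = 5 |
|---|---|---|---|---|
| 0 | 0% | 80.0% | 428 (0) | 79.5% |
| 0.02 | 1.0% | 80.8% | 437 (9) | 80.3% |
| 0.05 | 2.5% | 82.0% | 451 (23) | 81.5% |
| 0.10 | 5.1% | 84.0% | 476 (48) | 83.5% |
| 0.15 | 7.8% | 86.0% | 504 (76) | 85.6% |

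**Step 3: break-even.** Setting (1 − R²) × 425 / (425 − k) = 1 gives R² = k/425. That is 0.5% for k = 2 (age and APACHE II, one term each), 0.9% for k = 4 and 1.2% for k = 5. Below roughly 1% the adjustment costs a fraction of a power point; above it, the trial gains.

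**Step 4: chance imbalance.** With 428 patients the SD of a standardized baseline difference is 2/√428 = 0.097, with a 95% range of ±0.19. If the covariate correlates 0.1 to 0.4 with the baseline-adjusted outcome, an imbalance at the edge of that range shifts the estimate by about 0.02 to 0.08 residual SD. The standard error of the planned contrast is itself 0.097 residual SD and already contains this variation. The shift is therefore another view of the precision in Step 2 and must not be counted twice.

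**The case against.** The strongest case against is that nothing here is wrong. ANCOVA on the baseline value of the outcome is an accepted primary analysis. No stratification factor is stated, so none has been left out of the model. The gain rests wholly on an assumed R², which could be nil. The article is also condensed, and further adjusted models may stand in a fuller plan. All of this is right, and it limits the point to efficiency. It does not remove it: the stated primary model names one covariate, and a supporting analysis elsewhere would not change that.

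The contrast with duration is also weaker than it looks. The first test for duration is unadjusted, so a regression is its natural supplement, whereas severity is already adjusted for baseline.

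A reader might infer more than the document supports:
- **That chance imbalance biases the severity estimate.** Under randomization it does not; the standard error and p-value cover it.
- **That the article rules out any adjusted severity analysis.** The covariates of the mixed-effects model are unstated, and silence is not exclusion.
- **That ICU ward is a recorded covariate of proven value.** Ward is named only as an eligibility setting. Table 1 gives ICU mortality of 11%, 12% and 1.3% by unit, but for the general ICU population and for death, not for day-8 severity given baseline.
- **That age is shown to be prognostic because it sets the haloperidol dose** ("patients under the age of 60 years will be given 1 mg/dose, and those aged 60 years or older will be given 0.5 mg/dose"). That rule applies in the intervention arm. It bears on whether the effect differs by age, not on whether age predicts the score in both arms.
- **That the covariates are known to precede randomization.** The article says record data are collected at baseline and through the study, and gives no timing for APACHE II.

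**Conclusion.** The point holds as a possible loss of precision on one of the two primary outcomes. It is not bias, error or contradiction, and the planned ANCOVA would support a valid conclusion as it stands.

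Over the assumed range of R² the result runs from a loss of about half a power point to a gain of about six. The largest gain that this range allows equals about 76 extra patients. The size depends on two assumptions that the article cannot settle: the 80% starting power and the R² itself. The asymmetry is the reason to act, because the worst case is a fraction of a point and break-even lies near 1% of the remaining variance.

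**What to change.** Name the severity model in advance as day-8 DRS-R-98 severity score on arm, baseline score, age and APACHE II, with the form in which each covariate enters. Use only values fixed before randomization. Add ICU ward only as the ward at randomization, and only if it is recorded. Keep the baseline-only ANCOVA as a supporting analysis.

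For age and APACHE II the cost is wording and a few degrees of freedom, with no new data. APACHE II also needs two short rules: which time window counts as baseline, and how a missing value is handled (for example, the overall mean or a missing-value indicator).
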